### Intervention

Participants in both groups will receive structured rehabilitation interventions over an 8-week period, consisting of 5 sessions per week.

#### Comparison Group

Participants allocated to the comparison group will receive conventional rehabilitation therapy, including resistance stretching, joint mobility training, balance training, core stability exercises, and functional electrical stimulation. Each session will last approximately 120 minutes and be delivered once daily, 5 days per week.

#### Intervention Group

Participants in the intervention group will receive robot-assisted gait training combined with rTMS.

#### Pediatric Gait Rehabilitation Robot

Robot-assisted gait training will be delivered using the pediatric gait rehabilitation robot (BFR-K-A200; Chengdu Buffalo Robotics Technology Co). This device integrates an exoskeleton with a wheeled walker and incorporates adaptive gait assistance algorithms informed by individualized movement characteristics.

Each robot-assisted training session will last 30 minutes. Participants in the intervention group will receive 2 sessions per day (one in the morning and one in the afternoon), 5 days per week, for a total of 8 weeks (ie, 80 sessions). The total daily intervention time for robot-assisted training is 60 minutes. Training intensity and gait assistance parameters will be individualized according to participant tolerance and rehabilitation needs.

#### Repetitive Transcranial Magnetic Stimulation

rTMS will be delivered using a figure-of-eight coil, targeting the primary motor cortex (M1) according to the international 10-20 electroencephalography positioning system (Figure 3). Before the first rTMS session, each participant’s resting motor threshold will be determined as the minimum stimulus intensity required to elicit a motor-evoked potential of ≥50 μV in the contralateral first dorsal interosseous muscle in at least 5 of 10 consecutive trials. rTMS will be delivered at 90% of resting motor threshold. Each session consists of stimulation over the affected hemisphere M1 at 5 Hz, with a total of 1200 pulses delivered in a pattern of 2 seconds of continuous stimulation followed by 8 seconds of rest. This is followed by stimulation over the unaffected hemisphere M1 at 1 Hz, with a total of 900 pulses delivered in a pattern of 1 second of continuous stimulation followed by 2 seconds of rest. Total session duration is approximately 30 minutes. rTMS will be administered twice daily, 5 days per week.

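### The rTMS pulse counts, frequencies, on/off patterns and session length cannot all hold: as written the pulses take 65 minutes, while the session is given as about 30

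*Protocol article*

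**What the plan says.** All the stimulation figures stand in one section of the Protocol article, Repetitive Transcranial Magnetic Stimulation.

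- First block (5 Hz, affected side): "with a total of 1200 pulses delivered in a pattern of 2 seconds of continuous stimulation followed by 8 seconds of rest".
- Second block (1 Hz, unaffected side): "with a total of 900 pulses delivered in a pattern of 1 second of continuous stimulation followed by 2 seconds of rest".
- Length and frequency of sessions: "Total session duration is approximately 30 minutes. rTMS will be administered twice daily, 5 days per week".
- Order of the two blocks: "This is followed by stimulation over the unaffected hemisphere M1 at 1 Hz".

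The other daily times are given under Pediatric Gait Rehabilitation Robot ("The total daily intervention time for robot-assisted training is 60 minutes") and under Comparison Group ("Each session will last approximately 120 minutes and be delivered once daily, 5 days per week"). For the intervention group the article lists robot training and rTMS and no conventional therapy.

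**The concern.** Frequency, pulse count, on time and off time together fix how long a block lasts. The article gives all four for each block, says that one block follows the other, and then gives a session length. The length can therefore be checked, and it does not agree with the rest.

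rTMS is one of the two components of the experimental treatment. If its description contradicts itself, any session delivered departs from at least one written element. This has three consequences.

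- A reader cannot state or repeat the exposure.
- The weekly fidelity review (Quality Control, Treatment Phase) and the documentation of deviations (Treatment Adherence Monitoring) have no consistent standard to apply. Adherence is counted in completed sessions, yet the text gives two incompatible accounts of a complete rTMS session.
- If settings were not uniform, participants in the same arm may have received different stimulation. The daily time in the intervention arm is also left open.

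**Working it through.** **Inputs** (Protocol article, sections named above)

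- 5 Hz block: 1200 pulses, 2 s on, 8 s off.
- 1 Hz block: 900 pulses, 1 s on, 2 s off, after the 5 Hz block.
- Stated rTMS session: about 30 min, twice daily.
- Robot training: two 30-min sessions, 60 min per day.
- Comparison arm: about 120 min per day.

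**The article's own figures.** Robot time reproduces: 2 × 30 = 60 min per day. The rTMS session length does not, as follows.

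**Formula.** Block duration = [pulses ÷ (frequency × on time)] × (on time + off time). The two blocks are added because they run in sequence.

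- 5 Hz block: 1200 ÷ (5 × 2) = 120 trains; 120 × 10 s = 1200 s = 20 min.
- 1 Hz block: 900 ÷ (1 × 1) = 900 trains; 900 × 3 s = 2700 s = 45 min.
- Session: 20 + 45 = 65 min, which is 65 ÷ 30 = 2.2 times the stated length. The 1 Hz block alone exceeds the stated session by 15 min.

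**Other readings tried**

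| Reading | 5 Hz block (min) | 1 Hz block (min) | Session (min) | Keeps both stated patterns? |
|---|---|---|---|---|
| As written | 20 | 45 | 65 | yes |
| As written, last rest of each block dropped | – | – | 64.8 | yes |
| Pulse counted at both ends of each 1 Hz train only | 20 | 22.5 | 42.5 | yes |
| Pulse counted at both ends of every train | 18.2 | 22.5 | 40.7 | yes |
| 5 Hz block without rests | 4 | 45 | 49 | no |
| 1 Hz block without rests | 20 | 15 | 35 | no |
| Neither block with rests | 4 | 15 | 19 | no |

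The shortest session that keeps both patterns is 40.7 min, and it needs a generous way of counting pulses. The reading closest to 30 is 35 min, and it drops the 2 s rest that the text states.

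**If session length and patterns are both held.** After a full 5 Hz block, 30 − 20 = 10 min remain. At one pulse per 3 s, that allows 600 ÷ 3 = 200 of the 900 pulses at 1 Hz. This shows how far the pulse count would have to move under that one assumption. It is not a claim about what was delivered.

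**Daily time in the intervention arm** = 60 + 2 × rTMS session length

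- Stated 30 min holds: 60 + 60 = 120 min (600 min per week).
- 1 Hz rests not applied: 60 + 70 = 130 min (650 per week).
- Written pattern holds: 60 + 130 = 190 min (950 per week).

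Against about 120 min in the comparison arm, the difference is 0, about 10 or about 70 min per day.

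**The case against.** The strongest defence accepts the arithmetic and disputes what follows from it. Four stronger readings are tempting, and the article does not support them.

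- **That the arms were designed to have equal contact time and no longer do.** No section says so. The equality 60 + 60 = 120 is a sum made from the article's numbers. Strengths and Limitations already concedes that the groups differ in the structure and frequency of treatment. Equal minutes would not make the arms alike in any case, since half of the 120 minutes would be stimulation rather than exercise. What remains is that this concession does not mention total time, so a difference in time, if there is one, should be stated.
- **That sessions last 65 minutes and the arm receives 190 minutes a day.** This holds only if the written pattern is right and the session length is wrong. The article does not show which element is in error, so these figures are the upper end of a range.
- **That participants received different stimulation.** Nothing shows this. The study has one center, centralized training, standard operating procedures and weekly fidelity meetings. One uniform setting that the article misdescribes fits the text at least as well. Variation is a possibility to be checked.
- **That the primary analysis is undermined.** The endpoint, estimand, model and sample size do not depend on these figures, and the treatment-policy comparison can still be computed. What suffers is the description of the treatment being compared.

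None of this removes the contradiction. The word that qualifies the 30 minutes cannot cover a gap of 35 minutes, no other section resolves it, and the details are stated rather than left to a fuller document.

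**Conclusion.** The point stands as an internal contradiction in the specification of the experimental treatment. Pulse counts, frequencies, on/off patterns and session length cannot all be true: 65 minutes on the written pattern against about 30 stated. The 65 minutes follows from the article's own numbers and assumes only that a train delivers frequency × on time pulses and that the blocks run one after the other, as the text says. Counting pulses in the most generous way still leaves 40.7 minutes.

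The supported consequence is that the stimulation delivered cannot be identified, checked or replicated from this text. Intervention-arm time is uncertain between 120 and 190 minutes a day across the three scenarios computed. Because recruitment began in January 2025 and enrollment was still open in June 2026, this needs correcting now, although it may turn out to be only an error in the printed text.

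**What to change.** 1. Reconcile frequency, pulse count, on and off times and session length in the rTMS section against the settings actually programmed for participants treated since January 2025. Which parameter is right is for the clinical team, and none is proposed here.
2. Restate the rTMS session length and the total daily time in each arm. If the times differ, say so beside the existing limitation on treatment structure and frequency.
3. Record delivered pulses per block and minutes per session on the case report form, so that exposure can be reported as delivered.
4. If the settings differed between participants or over time, report this and describe the intervention by what was given.

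The cost is a check of device or treatment records, a correction to the text and a few extra fields on the case report form. No additional participants or visits are needed.

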**Figure 3 figure3:**
[figure not shown]
The international 10-20 electroencephalography system.

#### Concomitant Therapies

During the 8-week intervention period, participants in both groups will be asked not to receive any rehabilitation therapies outside the study protocol, as this would confound outcome interpretation. Any deviation from this requirement will be prospectively documented. Participants who receive substantial additional therapies (eg, more than 3 sessions) will be excluded from the per-protocol analysis but retained in the intention-to-treat analysis.

#### Safety Monitoring

Safety procedures will be implemented throughout all interventions, including joint screening, warm-up and cooldown exercises, equipment inspection, and continuous monitoring for adverse reactions.

Children with contraindications to rTMS will be excluded prior to treatment initiation. To monitor fatigue associated with repeated training sessions, the pediatric OMNI Rating of Perceived Exertion scale (0-10) will be administered before each intervention session. Treatment intensity will be modified or sessions postponed if participants report perceived exertion scores ≥7.

All adverse events, including skin irritation, pain, dizziness, nausea, falls, muscle twitching, or seizures, will be recorded using standardized case report forms. Serious adverse events will be reported to the institutional ethics committee within 24 hours and will prompt immediate clinical evaluation and consideration of treatment discontinuation.

#### Treatment Adherence Monitoring

Treatment adherence will be monitored throughout the 8-week intervention period using standardized attendance logs maintained by treating therapists. Attendance will be recorded at each scheduled treatment session and reviewed weekly by the study coordinator.

Adherence will be calculated as the proportion of completed sessions relative to the total number of scheduled sessions. Participants who attend less than 80% of the prescribed intervention sessions will be considered nonadherent and excluded from the per-protocol analysis but retained in the intention-to-treat analysis.

Any missed sessions, reasons for absence, and deviations from the intervention protocol will be documented prospectively. To enhance adherence, guardians will receive regular reminders and appointment confirmations during the study period.

### Outcome Measures

#### Primary Outcomes

The primary outcome of this study is the change in GMFM-88 score from baseline to week 8.

The GMFM-88 is a validated and widely used instrument for evaluating gross motor function in children with CP [18]. It comprises 88 items organized into 5 developmental domains, including lying and rolling; sitting; crawling and kneeling; standing; and walking, running, and jumping. Each item is scored on a 4-point ordinal scale (0-3), with higher scores indicating better motor performance.

The GMFM-88 was selected rather than the GMFM-66 because of its broader item coverage and greater sensitivity to functional change across heterogeneous CP populations with varying Gross Motor Function Classification System (GMFCS) levels.

#### Secondary Outcomes

##### Muscle Tone

Muscle tone will be assessed using the MAS, a commonly used clinical tool for evaluating spasticity [19]. MAS grades (0, I, I+, II, III, and IV) will be converted into ordinal scores (0-5) for statistical analysis, with higher scores indicating greater muscle tone.

##### Gait Performance

Gait performance will be evaluated using a 3D gait analysis system [20]. Reflective markers will be placed at standardized anatomical landmarks, and both static and dynamic gait data will be collected according to institutional gait laboratory protocols.

Participants will perform repeated walking trials at self-selected walking speed along a standardized walkway. Key gait parameters will include gait cycle duration, cadence, stance and swing phase duration, step width, and step length.

##### Electromyography Assessment

Electromyography assessments will be performed using the Nicolet EDX system (Natus Medical Incorporated, Pleasanton). Nerve conduction velocity, latency, and amplitude of the tibial, peroneal, and superficial peroneal nerves will be recorded.

### Sample Size Estimation

Sample size estimation was based on the primary outcome (change in GMFM-88 score at week 8). On the basis of a recent meta-analysis of noninvasive brain stimulation (including rTMS) in children with CP, which reported effect sizes ranging from 0.47 to 0.63 for GMFM outcomes [13], a moderate between-group effect size (Cohen *d*=0.60) was assumed for the primary outcome.

Using G*Power (version 3.1.9.7), with a 2-sided α level of .05 and 80% statistical power, the estimated minimum sample size was 46 participants per group. Allowing for an anticipated attrition rate of 15%, the final recruitment target was set at 54 participants per group, yielding a total sample size of 108.

### Quality Control

#### Design Phase

All investigators and therapists will undergo centralized training before study initiation. Standardized operating procedures will be implemented to ensure consistency in participant screening, intervention delivery, and outcome assessment.

#### Treatment Phase

Weekly multidisciplinary meetings will be conducted to review intervention fidelity, monitor protocol adherence, and address operational issues.

#### Data Management

Study data will be entered independently by 2 trained researchers using a double-entry system. Routine validation checks and discrepancy resolution procedures will be conducted to ensure data accuracy and integrity.

### Statistical Analysis

Statistical analyses will be conducted using SPSS (version 26.0; IBM Corp). A 2-sided α level of .05 will be adopted.

### Descriptive Analysis

Continuous variables will be summarized as means and SDs or medians and IQRs, depending on data distribution assessed using the Shapiro-Wilk test. Categorical variables will be summarized using frequencies and percentages.

#### Primary Estimand

The primary estimand is the between-group difference in the change in GMFM-88 score from baseline to week 8, in the target population of adolescents with spastic CP (GMFCS I-V, age 13-18 years), under the observed treatment conditions without intercurrent event adjustment (treatment-policy estimand).

#### Primary Analysis

The primary analysis will evaluate between-group differences in GMFM-88 change over time using a mixed-effects model for repeated measures. Fixed effects will include treatment group, time, and group-by-time interaction, while participant-level random effects will account for within-subject correlation. An unstructured covariance matrix will be specified.

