#### Covariates for Confounding Adjustment

Given the nonrandomized design, the following baseline covariates will be included in multivariable models and propensity score models: age, sex, GMFCS level, baseline GMFM-88 score, baseline MAS grade, and prior rehabilitation history.

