#### Propensity Score and Inverse Probability of Treatment Weighting

To further address confounding by indication, propensity score–based inverse probability of treatment weighting (IPTW) will be applied as a sensitivity analysis. Propensity scores will be estimated using a logistic regression model with group allocation as the dependent variable and the covariates listed above as predictors. After IPTW, balance will be assessed using SMDs, with an SMD<0.1 indicating acceptable balance. Covariate balance will be visualized using Love plots.

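### The primary mixed model names no confounder, and the promised covariate adjustment is not tied to the primary estimate of a guardian-preference study

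*Protocol article*

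**What the plan says.** In the protocol article, Study Design states that allocation follows guardian preference without randomization. Primary Outcomes fixes the endpoint: "The primary outcome of this study is the change in GMFM-88 score from baseline to week 8". Primary Estimand repeats it as a between-group difference.

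Primary Analysis specifies a mixed model for repeated measures on GMFM-88 change over time: "Fixed effects will include treatment group, time, and group-by-time interaction, while participant-level random effects will account for within-subject correlation". It adds: "An unstructured covariance matrix will be specified". No covariate is named there.

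Covariates for Confounding Adjustment then says that "the following baseline covariates will be included in multivariable models and propensity score models", and lists age, sex, GMFCS level, baseline GMFM-88, baseline MAS grade and prior rehabilitation history. It does not say which models are meant. The propensity score section states that "inverse probability of treatment weighting (IPTW) will be applied as a sensitivity analysis". Sensitivity Analyses lists a per-protocol and an IPTW analysis, and no separate covariate-adjusted one. Interpretation Within the Context of Study Design promises multivariable adjustment to reduce bias from nonrandom allocation.

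**The concern.** In a preference-allocated study the adjustment carries the comparison, so the reader must be able to see that the headline estimate is adjusted. Here the model statement and the covariate list stand side by side without a link. An analyst who follows Primary Analysis to the letter reports a crude contrast as the primary result. An analyst who reads the next section into it reports an adjusted one. Both can claim to have followed the protocol.

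The obvious repair, putting the six covariates into the stated model as main effects, may also do nothing. Assessments are at baseline, week 4 and week 8, so a three-level time factor is a natural reading. Under it, a table headed as adjusted could show the crude difference. The text does not settle whether the response is the score at all visits or the change score, so it cannot be told which case applies.

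**Working it through.** **1. The plan's own figure.** Sample Size Estimation works "with a 2-sided α level of .05 and 80% statistical power"; Cohen d=0.60 "was assumed for the primary outcome"; and "the estimated minimum sample size was 46 participants per group". A two-sample t test with d=0.60 needs 44.6, so 45 per group. Power is 80.4% at 45 and 81.2% at 46. The stated 46 is reproduced closely enough. That calculation is for an unadjusted, unconfounded comparison; 0.60 SD is the yardstick below.

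**2. Why main effects can cancel.** Let the response be the score at baseline, week 4 and week 8, with group G and a baseline covariate X as a main effect:

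Y(t) = a(t) + g(t)·G + b·X + e(t)

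Subtracting baseline from week 8:

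Y(8) − Y(0) = [a(8) − a(0)] + [g(8) − g(0)]·G + [e(8) − e(0)]

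The term b·X is the same at both visits and drops out. With complete data the estimated group difference in change is the same with or without X. It would also be the same within each dataset completed by the planned multiple imputation. With a covariate-by-time term, b depends on t and X stays in the change equation.

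**3. Simulation.** 300 trials per scenario, 54 per group, complete data, unstructured covariance, true effect 0. Assumptions, not from the documents: one confounder with an imbalance of 0.5 SD, a correlation of 0.4 with week-8 change, and half that effect on week-4 change. Cells give the mean week-8 estimate in SD of change, with the two-sided rejection rate.

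| Response | No covariates | Main effects | Covariate-by-visit |
|---|---|---|---|
| Score at three visits | 0.199 (17.7%) | 0.199 (17.7%) | −0.008 (5.7%) |
| Change at weeks 4 and 8 | 0.199 (17.7%) | 0.078 (8.0%) | −0.007 (5.3%) |

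In the first row the two left-hand estimates never differed by more than 1e-12 in any trial. The adjusted models in the second row also contain the baseline score. With imbalance 0.3 and correlation 0.3 the pattern repeats: 0.089, 0.089 and 0.003 for scores; 0.089, 0.039 and 0.004 for change. In the second row, what main effects leave behind comes from the covariate acting differently at the two visits.

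**4. Size of the crude bias.** In SD of change, bias = imbalance × correlation. At 46 per group, SE = √(2/46) = 0.2085, and type I error = P(|Z + bias/SE| > 1.96).

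| Imbalance | Correlation | Bias | Bias/SE | Type I error |
|---|---|---|---|---|
| 0.2 | 0.2 | 0.04 | 0.19 | 5.4% |
| 0.3 | 0.4 | 0.12 | 0.58 | 8.9% |
| 0.5 | 0.4 | 0.20 | 0.96 | 16.0% |
| 0.5 | 0.6 | 0.30 | 1.44 | 30.1% |

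Against the planned 0.60 this is 0.04/0.60 = 7% to 0.30/0.60 = 50%.

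**5. Covariance.** An unstructured residual matrix on three visits has 3 × 4/2 = 6 free parameters, which already describe every variance and covariance. A participant random intercept is a seventh and cannot be identified. On two visits the count is 3, and the intercept is a fourth. This applies only if the residual matrix is the one meant.

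**The case against.** The best defence is that the sections should be read together. The fixed effects are said to include three terms, which need not be a closed list. The covariate section follows directly and gives the nonrandomized design as its reason. IPTW is introduced as a further step, which presupposes an earlier one. No separate adjusted analysis is listed, so the primary model is the natural home for the covariates. Listing baseline GMFM-88 among them fits a post-baseline response, where main effects do help. The article also claims associations only and calls its findings hypothesis-generating, and an analysis plan may hold the details.

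Much of this stands, and it rules out several stronger readings that a reader might infer:

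- That the headline result is certainly unadjusted. This is the literal reading, not the only one.
- That main effects never matter. They are inert only when baseline is a repeated response; with change scores they cut the bias from 0.199 to 0.078 SD.
- That the group-by-time coefficient is the primary test, so that a change-score model would compare week 8 with week 4. No section says so, and the estimand points to week 8.
- That the model cannot be fitted. The sentence on the unstructured matrix follows the one on random effects and may describe their covariance.

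What the defence does not remove is the missing link. The article does state its primary model, and that statement does not carry the adjustment promised elsewhere. Cautious interpretation does not decide which estimate is primary.

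**Conclusion.** The point holds as a defect in how the primary model is fixed, not as proof that the result will be crude. The protocol admits at least two primary models. One of them keeps all the confounding that the text promises to reduce, and an obvious repair can leave that estimate unchanged. The cancellation is exact for complete data with baseline as a response and needs no assumption about confounding. The remaining bias with change scores depends on a covariate effect that differs between visits, as simulated.

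The sizes (0.04 to 0.30 SD; type I error about 5% to 30%) rest wholly on assumed imbalances of 0.2 to 0.5 SD and correlations of 0.2 to 0.6. At the lower end the effect is slight. The documents do not support naming one value within that range.

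**What to change.** State one adjusted primary model before the data are analysed:

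- Response: GMFM-88 change (or score) at weeks 4 and 8.
- Fixed effects: group, visit, group-by-visit, and each of the six listed covariates with its visit interaction.
- Primary estimate and test: the adjusted group difference at week 8.
- Covariance: say whether the unstructured matrix is the residual or the random-effects matrix. If residual, drop the participant random intercept.
- Keep IPTW as the sensitivity analysis and show the crude model as supportive only.

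A model that keeps baseline as a response and omits baseline adjustment should not be presented as equivalent. If change depends on the baseline score and the groups differ at baseline, the two give different answers, and baseline GMFM-88 is one of the plan's own named confounders.

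The cost is wording and some degrees of freedom. With GMFCS as five categories (four terms) and one term for each of the other five covariates, that is 4 + 5 = 9 covariate coefficients per visit among 108 participants. No new data are needed.
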